#### Aim 2: implementation: How do teachers use TeachTown, and what factors are associated with its use?

We will measure implementation of the TeachTown program using a subset of the implementation outcomes described by Proctor and colleagues [53]. Specifically, we will measure teachers’ fidelity to the program manual and penetration of use across classrooms. We hypothesize that the percentage of students using TeachTown and fidelity will vary among teachers and over time. Both will be influenced by teachers’ intentions to use TeachTown and determinants of those intentions (attitudes, norms, and self-efficacy). Because this aim focuses on teacher behavior (rather than student outcome), we aggregate penetration and fidelity to the teacher level.

### Measures

#### *TeachTown penetration*

Teachers’ use of TeachTown will be measured using the logs the TeachTown software produces.

#### *TeachTown Fidelity*

Teachers’ accurate use of TeachTown will be measured monthly via direct observation by coaches from the TeachTown program using a fidelity checklist created by the program developers.

### Independent variables

#### *Measures of intention and determinants of intention*

A questionnaire will use validated, standardized item stems to measure intentions, attitudes, norms, and self-efficacy regarding use of TeachTown online and offline (separately). The stems for each question were designed to be adapted for study of any behavior and have been used to successfully predict a large variety of behaviors [54–59].

*Teachers’ intentions* to use TeachTown online and offline components for instruction of students with ASD will be measured by two items (e.g., “How likely is it that you will use TeachTown for online instruction of students with ASD?”). Scaled response options will range from 1 (very unlikely) to 7 (very likely). If highly correlated, the two measures of intention will be aggregated for each behavior.

*Teachers’ attitudes,* or the extent to which one “likes” or “dislikes” using TeachTown components, will be measured by six (7-point) bipolar adjective scales, scored −3 to +3. For example, scales will allow respondents to rate using a TeachTown component as extremely unpleasant–extremely pleasant and as extremely wise–extremely foolish. The mean score across the six items will constitute our measure of attitudes toward using a TeachTown component.

*Teachers’ perceived norms* will be measured using two standard measures that capture perceptions of normative pressure. For example, respondents will be asked to rate on a 7-point scale the perception that most autism support teachers will use TeachTown online. If highly correlated, the two measures will be aggregated.

*Teachers’ self efficacy* will be measured by asking respondents to rate, on a 7-point scale, the statement, “If I really wanted to, I could use TeachTown online in my classroom” as likely/unlikely.

*Other covariates of interest* include years of teaching experience (measured through self-report) and staff-to-child ratios in the classroom (measured through direct observation).

### Data collection

The TeachTown company will provide anonymized monthly data on all students’ use of TeachTown. These data, aggregated to the classroom level, will allow us to measure penetration for all students in the classroom. Independent variables, including intentions and determinants of intention, will be measured immediately following the 2-day TeachTown training, so that teachers will have familiarity with the program before answering these questions.

#### Aim 3: exnovation: How does use of existing EBPs change when TeachTown is introduced, and what factors influence this change?

We hypothesize that (1) teachers will decrease the amount of one-to-one teaching incorporated into their daily schedules; (2) teachers will collect less data regarding student performance; and (3) the amount of positive reinforcement, behavior correction, and visual schedules provided by teachers will remain the same. We also will test the hypothesis that TeachTown facilitates EBP use by providing unsupervised instruction for some students, and therefore moderating the association between intentions and use of TeachTown. We will examine whether current EBPs are facilitated or exnovated when TeachTown is introduced and use qualitative methods to understand stakeholder perspectives of exnovation, if relevant. In separate analyses, we will examine whether use of TeachTown affects intentions to use EBP and determinants of those intentions: attitudes, norms and self-efficacy.

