For the past 8 years, our team has provided extensive training and coaching to autism support teachers in the use of several EBPs for children with ASD. The second set of hypotheses relate to teachers’ use of the EBPs in which we have trained them (aim 3). For this aim, we conceptualize TeachTown as a new technology that affects the organizational context and teacher behavior. TeachTown may influence teachers’ attitudes, norms, and self-efficacy about the use of existing EBP (pathway A) and moderate the association between their intentions to use these practices and their behavior (pathway B). Specifically, we hypothesize that introducing TeachTown will negatively affect teachers’ attitudes, norms, and perceptions about using existing EBP, and that teachers will “exnovate” existing practices when they adopt TeachTown. Exnovation refers to the “process whereby an organization decides to divest itself of an innovation that it had previously adopted.” [33–35] Introducing a new technology may result in one of three exnovation outcomes: full exnovation (the new technology completely replaces the previous one so that there is no trace of the previous practice), partial exnovation (the new technology replaces parts or components of the previous practice), or no exnovation (the new technology does not replace the previous practice). We hypothesize that the introduction of TeachTown will result in partial exnovation of EBPs. Teachers may reduce their use of EBP because they think that TeachTown is a reasonable (and easier) substitute for practices like one-to-one instruction or data collection. Our second competing hypothesis is that introducing TeachTown changes the organizational context by giving teachers a tool to provide unsupervised instruction to some students, which would increase the time the teacher has to work with other students. In this case, we would expect use of EBP to increase in classrooms with TeachTown.

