#### *Quantitative data analysis*

The quantitative analysis will take place in three parts, each addressing one of the questions of interest. To address the question of whether TeachTown results in reduced use of EBP, we will compare the intervention and control groups in year 1. We will conduct the analysis at the teacher level. We will create three fidelity variables for each of the five EBPs, as we did in aim 2. The analyses will mirror those described in aim 2. To address the question of whether introducing TeachTown affects intentions to use EBPs, we will conduct similar analyses with intentions to use each of the EBPs at time 2 as the outcomes of interest. If intentions are determined to vary as a function of TeachTown use, we then will explore the effects of TeachTown on each of the determinants of intention.

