#### *Statistical power for quantitative analyses*

The prior trial of TeachTown reports that students made gains in communication skills of a moderate effect [71]. Meta-analytic reviews of studies of other interventions for children with ASD report large intervention effects [4, 72–74]. Based on this literature, we conducted a power analysis to determine the effect sizes we could expect in our cluster randomized study of students nested within the 70 classrooms in the district. Using the Power and Precision software package [75], we calculate that for student outcomes we will have power of 80% to detect a moderate intervention effect of *d* = 0.43, assuming enrollment of four students per classroom, an intraclass correlation (ICC) of 0.2, and inclusion of one covariate in our regression model that explains 15% of the variation. For teacher outcomes, we will have 80% power to detect a larger effect of the intervention (*d* = .7) assuming a model with a single covariate (*r*
^2^ = .15). All models assume two tailed tests with alpha = 0.05.

Our secondary goal is to test the potential impact of moderating factors. With the proposed sample size, the study will have power of 80% to identify an effect size associated with moderators of *d* = 0.65 [71], a moderate-to-large effect. For teacher-level analyses, we are powered to test moderators with an effect size of *d* = 0.85, a large effect.

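### Aim 3 predicts that some practices will not change, but the stated analysis tests only for a difference and is sized for d = 0.7, so it cannot support that prediction

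*Protocol article*

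**What the plan says.** The opening paragraph of Aim 3 gives three numbered hypotheses. The first two predict decreases, in one-to-one teaching and in data collection. The third predicts no change: "the amount of positive reinforcement, behavior correction, and visual schedules provided by teachers will remain the same".

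Under the Aim 3 heading Quantitative data analysis, the comparison is framed as a question about a decrease: "To address the question of whether TeachTown results in reduced use of EBP, we will compare the intervention and control groups in year 1". It is made at the teacher level, and on method the section adds "The analyses will mirror those described in aim 2". The Aim 2 methods are Poisson regression, growth-mixture and multinomial models, structural equation modelling and ordinal logistic regression.

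Statistical power for quantitative analyses states "For teacher outcomes, we will have 80% power to detect a larger effect of the intervention", with the effect given as d = 0.7 and a single covariate with r² = 0.15. It closes with "All models assume two tailed tests with alpha = 0.05".

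**The concern.** A prediction of no change and a test of a difference answer different questions. Failing to reject a zero difference is what one expects when nothing changed, but also when the study is too small to see a change that did occur. None of the Aim 2 methods that Aim 3 borrows is an equivalence method, and the article gives no numerical meaning to unchanged.

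This matters because the Background presents reduced use of existing practices as a possible harm of TeachTown, to be weighed against its benefit. For reinforcement, correction and visual schedules, no change is the reassuring answer. As the analysis is described, nothing separates evidence for that answer from lack of evidence against it.

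**Working it through.** **Inputs.** 35 TeachTown and 34 control classrooms (Aim 1, Data analyses). Two-sided alpha 0.05, d = 0.7 and r² = 0.15 (Statistical power for quantitative analyses). Differences are in SD units of the outcome. I treat the comparison as a two-group comparison of teacher means and give each result twice: without credit for the covariate, then with the residual variance reduced by 15%.

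**1. The plan's own figure.** Noncentral t power at d = 0.7 is 81.7% without covariate credit and 87.4% with it. The stated 80% is reproduced on the first reading and is conservative on the second.

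**2. Precision.** SE = SD × √(1/35 + 1/34).
- No credit: SE = 1 × 0.241 = 0.241. The 95% half-width is 1.996 × 0.241 = 0.48 SD.
- With r² = 0.15: SE = √0.85 × 0.241 = 0.222. The 95% half-width is 1.997 × 0.222 = 0.44 SD.

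An estimate of exactly zero would still be compatible with a fall of 0.44 to 0.48 SD.

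**3. Chance that a real fall is non-significant** (1 − power, noncentral t).

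| True fall | No covariate credit | r² = 0.15 |
|---|---|---|
| 0.3 SD | 77% | 73% |
| 0.4 SD | 63% | 57% |
| 0.5 SD | 47% | 40% |
| 0.7 SD | 18% | 13% |

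**4. What an equivalence criterion could deliver.** Two one-sided tests at 0.05 are the same as requiring the 90% interval to lie inside ±M. With a true difference of zero, power ≈ 2Φ(M/SE − t₀.₉₅) − 1, with t₀.₉₅ = 1.668.
- M = 0.7, no credit: 0.7/0.241 = 2.907, and 2Φ(1.239) − 1 = 78%.
- M = 0.7, r² = 0.15: 0.7/0.222 = 3.153, and 2Φ(1.485) − 1 = 86%.
- M = 0.5: 32% and 44%.
- M = 0.4: 0% and 11%.

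For 80% power at M = 0.5 the trial would need about 69 teachers per arm, or 59 with r² = 0.15.

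**5. The price of a wide margin.** With M = 0.7 and a true fall of 0.4 SD, the 90% interval would still lie inside the margin about 34% of the time without covariate credit and 38% with it (simulated, with the SE estimated from the data).

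**The case against.** The best reply is that the article never promises to confirm a null. It frames the arm comparison as a question about reduced use, Aim 3 is not the primary outcome, and a margin may sit in an analysis plan that is not shown. Aim 3 also includes trajectory models, analyses of intentions and an interview arm that is weighted equally with the quantitative data. Two-tailed testing is itself sensible, because the Background allows for use of existing practices to rise.

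Much of this stands and limits the weight of the point. It does not remove it: the article states both a no-change hypothesis and an inference, and the second cannot support the first. Interviews about teachers' views cannot establish that observed amounts were unchanged.

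Two stronger readings are tempting, and the article supports neither.

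- **Fixed reading rules.** A reader might infer that a non-significant result will be reported as no exnovation and any single significant one as partial exnovation. No section says so. The Background defines the categories in words, for example "partial exnovation (the new technology replaces parts or components of the previous practice", and ties them to no test result.
- **Multiplicity.** The analysis section says "We will create three fidelity variables for each of the five EBPs, as we did in aim 2", which makes 3 × 5 = 15 variables. A reader might conclude that a false finding is more likely than not, since 1 − 0.95¹⁵ = 54%. That requires independent tests. The figure is about 36% at a pairwise correlation of 0.5 and 20% at 0.8. Counting only false decreases, it is about 32%, 18% and 10% at correlations of 0, 0.5 and 0.8. The expected decreases are named in advance, the no-change hypothesis concerns two of the five practices (about 6 of the 15 variables), and a multiplicity rule for a non-primary aim may properly be left to the analysis plan.

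**Conclusion.** The point holds for the third Aim 3 hypothesis and no further. As stated, the analysis can detect a large change in these practices but cannot support the claim that they did not change. A true fall of 0.4 SD would be non-significant in roughly six trials out of ten (57 to 63%), and the 95% interval spans about ±0.44 to ±0.48 SD.

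These figures assume a two-group comparison of teacher means with all 69 classrooms analysed. Repeated observations could narrow the intervals, and missing classrooms would widen them. The 0.4 SD fall and all equivalence margins are illustrations of mine. The article calls no particular fall harmful and gives no margin.

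**What to change.** For positive reinforcement, behavior correction and visual schedules, report the between-arm difference in year 1 with its confidence interval. Then choose one of two options:

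1. State and justify a margin before the data are seen. Claim no change only if the 90% interval lies inside it, and otherwise report the result as inconclusive.
2. Reword the hypothesis as no decrease expected, reported with intervals, and make no claim of equivalence.

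Under the first option, say openly that the design has adequate equivalence power only near 0.7 SD. That margin is wide: it would still pass a true 0.4 SD fall about a third of the time. The interval should therefore always be shown beside the label. Also name the variable to which the margin applies. The hypothesis concerns amounts of reinforcement and correction, but the Dependent variables section scores reinforcement as praise divided by correction, and that ratio can stay constant while both amounts fall.

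The cost is analysis wording and the work of justifying a margin, with no new classrooms or data. The real downside is that at margins of 0.5 SD or less, most results would be inconclusive even if nothing had changed.

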### Overview of current EBPs

As part of our ongoing training and consultation efforts, we train and consult to teachers in five EBPs that are common across most classroom-based autism interventions: discrete trial training, pivotal response training, data collection, positive reinforcement for classroom management, and visual schedules.

*Discrete trial training* is implemented using an intensive one-to-one teaching session in a setting free from distractions. Discrete trial training generally involves the repeated practice of the same response for several successive teaching episodes, breaking down complex skills into component parts, and the use of reinforcers that are functionally unrelated to the response (e.g., providing a token for correctly identifying a car).

*Pivotal response training* uses one-to-one teaching but relies on a less structured teaching environment. It consists of loosely structured sessions that are initiated and paced by the child, take place in a variety of locations, and employ a variety of stimuli. For example, in a situation in which the student wants to play with a toy, he must explicitly request the toy from the teacher.

*Classroom data collection* is a critical component of autism intervention. Each teaching strategy has data sheets to track responses during one-to-one teaching and levels of prompts needed during daily routines.

*Positive behavior support for behavior management* comprises class-wide behavior management techniques. The goal of these strategies is to prevent challenging behavior before it occurs and maximize opportunities for learning. Positive behavior support strategies include the use of visual supports, clear and concrete instructions, timers and cues to signal transitions, and high rates of positive reinforcement for desired behavior paired with low rates of behavior correction for undesired behavior.

*Visual schedules* are used throughout the day. A daily visual schedule for each child is posted in prominent locations and reviewed daily. Visual schedules are used to increase independence and decrease frustration during transitions.

#### Quantitative approach

To examine changes in the use of EBP as a result of TeachTown, we will compare the use of EBP in the TeachTown group and control group in year 1. To address the questions of (1) whether increased use of TeachTown results in changes in the use of EBP, (2) TeachTown implementation changes intentions to use other EBP, and (3) whether TeachTown moderates the association between intentions and use of EBPs, we use data from year 1 for the intervention group and year 2 for the waitlist control, so measures will be from the first year that each classroom implements TeachTown.

### Quantitative measures

#### Dependent variables

Accuracy of EBP implementation will be assessed every other month through direct observation in each classroom using fidelity checklists which comprise the most commonly used fidelity measures for these intervention techniques. [52, 62–64] Bachelor’s level research assistants will be trained to 90% reliability on each fidelity measure through didactic instruction and coding of training videos prior to conducting any observations in the field.

*Delivery of one-to-one instruction: discrete trial training and pivotal response training* will be measured through teacher report and direct observation by trained RAs. How much each is used with each student will be measured through teacher report. We will measure accuracy of discrete trial training through monthly direct observations using a fidelity checklist. We will examine quantity and accuracy separately as dependent variables. We also will examine the product of “quantity × accuracy” consistent with our previous evaluations of fidelity for these EBPs [64].

*Data collection* will be measured through observation of completed data sheets. Trained research assistants will record the occurrence of data collection by recording the amount of data collected for each child since the last observation, based on the number of completed data sheets present.

*Positive behavior support strategies* will be measured through direct observation of teacher behavior during regular instructional routines by trained research assistants. RAs will measure teacher’s use of positive reinforcement for desired student behavior using a tool designed to record the amount of praise and behavior correction statements provided by teachers during a 10-min structured observation [65]. Reinforcement will be calculated as a ratio (i.e., the number of praise statements divided by the number of correction statements).

*Visual schedules* will be measured monthly by trained RAs through direct observations based on a fidelity checklist. Use of schedules will be calculated as a ratio of the teacher’s correct use of schedules for each student divided by the total number of students.

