TeachTown may be a feasible intervention that improves outcomes for children with ASD in public schools that is well suited for under-resourced settings. On the other hand, there may be negative consequences of implementing CAI, such as reduced use of existing EBPs, which should be weighed against potential benefit. The proposed study offers a novel opportunity to test the effectiveness and implementation of a promising CAI and concurrently increase our understanding of what happens to existing practices when new ones are introduced. Accordingly, we rely on a hybrid effectiveness-implementation design [36], in which the primary outcome is effectiveness, but where we also examine the association of organizational and teacher characteristics with TeachTown and EBP implementation.

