### Measures

Our primary outcome of interest, in keeping with recent randomized trials of autism interventions, is cognitive gain. Other selected measures are tied to the domains in which TeachTown purports to affect change (see Table 1).

**Table 1 Tab1:** List of measures, respondents, and time points for data collection

Measure	Respondent	Time point
Aim 1: Effectiveness		
Differential Ability Scales, 2nd Edition (DAS-II)	Direct observation of student functioning completed by graduate student or clinician	Beginning and end of year 1
Bracken Basic Concept Scales, 3rd Edition	Direct observation of student functioning completed by graduate student or clinician	Beginning and end of year 1
Autism Diagnostic Observation Schedule—2nd edition (ADOS-2)	Direct observation of student functioning completed by graduate student or clinician	Throughout year 1
Adaptive Behavior Assessment System, 2nd Edition (ABAS-II)	Teacher rating form of child functioning	Beginning and end of year 1
Pervasive Developmental Disorder Behavior Inventory (PDD-BI)	Teacher rating form of child functioning	Beginning and end of year 1
Social Communication Questionnaire (SCQ)	Parent rating form of child functioning	Beginning of year 1
Family Demographic Questionnaire	Parent	Beginning of year 1
Teacher Demographic Questionnaire	Teacher	Beginning of year 1
Aim 2: Implementation		
TeachTown penetration	Computer software logs	Monthly
TeachTown fidelity	Direct observation of teacher behavior conducted by TeachTown staff	Monthly
Intentions and attitudes scale	Teacher rating scale	Mid-year years 1 and 2
Aim 3: Exnovation		
Existing EBP fidelity	Direct observation of teacher behavior conducted by trained research assistants	Monthly

*Cognitive ability* will be assessed using the Differential Ability Scales, 2nd Edition (DAS-II) [41]. The DAS-II assesses cognitive abilities that are important to learning and may be administered to children ages 2 years 6 months through 17 years 11 months across a broad range of developmental levels. A member of the assessment team will administer the DAS-II to students in the study at the beginning and end of the academic year in year 1.

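### Observation of existing EBPs is set at two different frequencies, and the data-collection outcome is a count since the previous visit that is not scaled to elapsed time

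*Protocol article*

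**What the plan says.** The frequency of EBP observation appears in four places in the protocol article.

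- Aim 3, Dependent variables, opening sentence: "Accuracy of EBP implementation will be assessed every other month through direct observation in each classroom using fidelity checklists".
- Same section, one-to-one instruction: "We will measure accuracy of discrete trial training through monthly direct observations using a fidelity checklist".
- Same section, visual schedules: these "will be measured monthly by trained RAs through direct observations based on a fidelity checklist".
- Table 1 (under the Aim 1 Measures heading), in the Aim 3 row for fidelity to existing EBPs: the method is "Direct observation of teacher behavior conducted by trained research assistants" and the time point is monthly.

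The data-collection outcome is defined in the same Dependent variables section. Research assistants note its occurrence by "recording the amount of data collected for each child since the last observation, based on the number of completed data sheets present". No frequency is attached to this measure.

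The outcome serves a stated hypothesis of Aim 3, that "teachers will collect less data regarding student performance". The main comparison is given under Quantitative data analysis: "To address the question of whether TeachTown results in reduced use of EBP, we will compare the intervention and control groups in year 1". The end of the Background explains why it matters: "there may be negative consequences of implementing CAI, such as reduced use of existing EBPs, which should be weighed against potential benefit".

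**The concern.** There are two linked problems.

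First, the opening sentence and the discrete trial training sentence describe the same construct (accuracy), the same method (direct observation) and the same kind of instrument (a fidelity checklist), yet give different frequencies. A field team cannot follow both. The choice fixes how many repeated measures each classroom contributes. The Aim 3 analyses are said to mirror those of Aim 2, which model fidelity trajectories, and the Aim 1 moderator analysis also uses trajectories of EBP fidelity.

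Second, a count accumulated since the previous visit grows with the gap between visits. Two other measures in the same section, reinforcement and visual schedules, are defined as ratios; this one has no denominator for time. If gaps vary, for instance after a missed or rescheduled visit, a change in the count may reflect the calendar and not the teacher. The first visit also has no previous visit from which to count.

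At stake is the reading of one exnovation hypothesis, on a consequence that the authors say should be weighed against benefit. The primary outcome, cognitive gain on the DAS-II, is not affected.

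**Working it through.** The plan gives no figure on this point to reproduce. The check is a comparison of the texts plus simple arithmetic.

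**Step 1. Frequencies side by side**

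| Place | What is observed | Frequency |
|---|---|---|
| Dependent variables, opening | accuracy of EBP implementation in general, by checklist | every other month |
| Dependent variables, one-to-one instruction | discrete trial training accuracy, by checklist | monthly |
| Dependent variables, visual schedules | schedules, by checklist | monthly |
| Table 1, Aim 3 row | fidelity to existing EBPs in general | monthly |
| Dependent variables, data collection | completed sheets per child | none stated |

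The first and fourth rows are both general statements and they disagree. The first and second disagree on the same construct and method.

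**Step 2. Observations per classroom**

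The length of the school year is not given, so 8 to 10 months is an assumption. Visits = months / interval, rounded down.

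- Monthly: 8, 9 or 10 visits for 8, 9 or 10 months.
- Every other month: 4, 4 or 5 visits.

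The number of points available for each trajectory is therefore about halved under the sparser reading.

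**Step 3. Count per visit**

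Expected count = monthly rate × months since the previous visit. The rate is not in the document; 5, 10 and 20 sheets per child per month are assumptions.

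| Assumed rate per month | Count after 1 month | Count after 2 months | Ratio |
|---|---|---|---|
| 5 | 5 | 10 | 2 |
| 10 | 10 | 20 | 2 |
| 20 | 20 | 40 | 2 |

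The ratio is 2 (log 2 = 0.69) at any constant rate, with no change in the teacher's behaviour.

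**Step 4. When this matters**

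- One uniform interval: both arms are multiplied by the same factor. The ratio of arms is unchanged and the comparison is not biased.
- Unequal gaps unrelated to arm: at 10 sheets per month, a one-month gap followed by a two-month gap gives counts of 10 and then 20, an apparent doubling at constant practice. This is noise in the trajectory.
- Gaps that differ by arm: the difference in gaps enters the arm contrast as bias.
- Gaps that differ by year: under Quantitative approach, three questions use year 1 for the intervention group and year 2 for the waitlist group. A difference between years would then coincide with arm.

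**Step 5. After scaling**

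Count / elapsed time gives 10 / 1 = 10 and 20 / 2 = 10 per month. The outcome is the same under either schedule.

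**The case against.** **General rule with exceptions.** The two monthly sentences could be read as exceptions to a two-monthly rule. This does not hold, because Table 1 is also general and says monthly.

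**Accuracy versus count.** The two-monthly sentence concerns accuracy scored by checklist, and the sheet count is a different kind of measure. This stands: the interval for the count is unspecified, not set twice, and the two problems should be kept apart.

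**Recording versus analysis.** The text says what assistants write down, not that the raw count is the analysis variable, and a full analysis plan may scale it. This stands in part. The explicit count outcome in Aim 2 has a log offset, but that offset is class size and gives no assurance about time. A later plan could settle the scaling; it would not remove the conflict between the stated frequencies.

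**Stronger readings that the document does not support.**

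- A reader might infer that some classrooms, or one arm, are observed monthly and others every other month. No section says so. The main comparison is concurrent in year 1, and the opening sentence applies its frequency to every classroom.
- A reader might suspect that monthly TeachTown visits disturb observation in the intervention arm. Those visits are made by the program's own staff, EBP observation by research assistants, and nothing says that one displaces the other.
- A reader might suppose that halving the visits costs precision on the sheet count as it can for snapshot measures. The count is cumulative: over an assumed 10 months at 10 sheets per month, 10 × 10 = 100 and 5 × 20 = 100 cover the same period.

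The Background speaks of negative consequences and also states a competing hypothesis that EBP use will rise. The outcome should not be presented as an established harm.

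**Conclusion.** The contradiction in observation frequency is certain on the current text and must be reconciled. Its size is 8 to 10 against 4 to 5 observations per classroom, assuming a school year of 8 to 10 months.

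The data-collection outcome as worded scales with the gap between visits, by a factor of 2 for two months against one, assuming a constant rate. That is a weakness of definition and not a demonstrated bias: with one uniform interval the year 1 comparison of arms is sound. The risk is noise from unequal gaps, and bias only where gaps differ by arm, or by year in the analyses that draw the two groups from different years.

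The point concerns a non-primary aim. It deserves correction because the count bears directly on a stated hypothesis and the remedy is cheap.

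**What to change.** 1. Reconcile the Aim 3 Dependent variables section and Table 1 to one observation interval for existing EBPs, applied in both arms. Which interval is for the study team to choose.
2. State that the same schedule governs the data-sheet count, and record the date of every visit.
3. Define the data-collection outcome as completed sheets per child per school day since the previous visit, or model the count with the log of elapsed school days as an offset. For the first visit, count from a fixed start date common to all classrooms.

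The cost is a wording correction, recording visit dates (the document does not say that they are already kept), and a small amount of extra analysis to convert dates to school days. No visits are needed beyond the schedule chosen.
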